**Studies on the Management of Trachomatous Trichiasis**

**Analytical Plan for Trial 2: Randomized controlled trial of immediate surgery vs. epilation for Minor Trichiasis**

**1. Participant flow**

*a) Eligibility, enrolment and follow-up*

The following will be shown by trial arm in a flowchart following CONSORT guidelines for non-inferiority trials (JAMA 2006: 295:1152-1160): Numbers eligible, consenting to take part, randomized, and who received the intended treatment. The numbers still in follow-up, censored, defaulting, and permanently lost-to-follow-up respectively at each visit will also be shown by arm. Reasons for declining to take part, not having surgery, or discontinuing follow-up will be summarized by arm.

*b) Censoring*

Patients in both arms will be considered as failures and immediately censored when they present with 5+ lashes in the trial eye. In addition, patients who present having had surgery (or repeat surgery) on the trial eye from other providers will be considered as failures and immediately censored.

1. **Description of baseline data**

The following characteristics of participants at baseline will be tabulated by arm:

- 1. Socio-demographic factors: age, sex, literacy, ethnic group.
  2. Behavioural factors: epilation habits, whether surgery has previously been offered, reasons for not having surgical treatment previously.
  3. Clinical status: trichiasis, entropion, inflammation, conjunctivilisation of lid margin, corneal scarring, evidence of epilation, visual acuity, symblepharon.

The distributions of these variables by treatment arm will be compared, to assess whether there is imbalance at baseline in these potential confounding factors.

1. **Primary outcome**

*a) Definition*

The primary outcome measure will be the proportion of participants with 5 or more lashes touching the eye on one or more follow-up visits. Lids with eyelash stubs which are not in contact with the eye will not be considered a treatment failure.

*b) Justification of primary outcome measure*

Trichiasis (lashes touching the eyeball) causes visual loss through corneal opacification. The purpose of the interventions being compared in this trial is to stop eyelashes touching the eyeball. It is anticipated that some of the patients in the surgery arm of the trial may commence epilation if their surgery fails. From an ophthalmic public health perspective they are ‘successes’ if they successfully prevent eyelashes touching the globe, despite the surgery itself having not been totally successful.

Previous studies have used a cut-off of 5 or more lashes for determining treatment choices (Arch Ophth 2006; 124: 309-314). Similarly, this level has been used in national blindness control programmes (The Gambia) as an indication for surgery.

*c) Sample size*

Our sample size of 1300 trial participants would provide 90% power to detect non-inferiority, assuming 10% loss to follow-up over 2 years, a 5% failure rate in the surgery arm, and non-inferiority margin of 10%. (i.e we would conclude non-inferiority if the upper 95%CI for the observed difference in failure rates was less than 10%)

The power to detect non-inferiority under different assumptions with this sample size is shown in the table below

**Table 1:** Power for detecting non-inferiority under different assumptions with sample size of 585 per arm (1300 recruited, 10% loss to follow-up)

| **Proportion failing in surgery arm (**[figure not shown] | **Proportion failing in epilation arm (**[figure not shown] | **Difference in proportions (**µ) | **Inferiority margin (**Δ) | **Power** |
| --- | --- | --- | --- | --- |
| 2% | 6% | 4% | 8% | 93% |
| 2% | 8% | 6% | 10% | 89% |
| 3% | 6% | 3% | 8% | 98% |
| 3% | 9% | 6% | 10% | 85% |
| 4% | 8% | 4% | 8% | 82% |
| 4% | 8% | 4% | 10% | 99% |
| 4% | 9% | 5% | 10% | 94% |
| 5% | 9% | 4% | 8% | 76% |
| **5%** | **10%** | **5%** | **10%** | **90%** |
| 8% | 11% | 3% | 8% | 83% |
| 8% | 12% | 4% | 10% | 93% |

*d) Statistical analysis*

Statistical analyses will calculate the difference in proportion failing in the two arms, and 95%CI for this difference using exact methods. Non-inferiority of epilation will be shown if the upper two-sided 95%CI around the estimated difference in proportions is below 10%. Blinded analyses conducted at the end of the trial showed an overall failure rate of 8%. Table 2 shows conclusions for different assumptions of the proportion failing in the surgery and epilation arm respectively. Given an overall failure rate of 8%, the conclusion will be that epilation is non-inferior to surgery if the proportion failing in the surgery arm is greater than 4.5%. Epilation will be deemed inferior, if the failure rate in the epilation arm is 15% or higher.

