**Secondary outcomes**

1. *Number of lashes touching the eye at each visit.*

This will include data from all time points. We expect a large proportion of individuals with no lashes touching, and will thus use a random effects zero-inflated Poisson analysis (Lee et al, Statistical Methods in Medical Research 2006:15:47-61). This model is suitable for count data with an excess of zeros, and adjusts for within-patient correlation. The model will provide a coefficient, 95%CI and p-value for the difference in log mean number of lashes in the intervention versus control arms.

1. *Lashes touching the cornea:*

The number of lashes touching just the cornea will be compared between the two arms of the trial. Lashes that only touch the peripheral eyeball (i.e. the sclera rather than the cornea), are probably not of great visual or pathological significance. This will be analysed with similar methods to that for the total number of lashes touching the eye at each visit.

1. *Entropion grade*

The effect of the intervention on the degree of entropion at 24 months will be analysed by ordered logistic regression.

1. *Conjunctivilisation of the lid margin grade*

The effect of the intervention on the degree of conjunctivilisation at 24 months will be analysed by ordered logistic regression.

1. *Corneal opacification*
   1. Descriptive measures of the baseline severity of CO
   2. Description of the change in CO between baseline and one and two year follow up time-points.
   3. Ordinal logistic regression analysis for change in CO category at one year and two years respectively, to identify factors associated with it, such as inflammation.
   4. The effect of the intervention on the degree of change in CO between baseline and 24 months will be analysed by ordered logistic regression.
2. *Visual acuity*

The effect of the intervention on the visual acuity (logMAR score) at 12 and 24 months will be analysed by linear regression.

1. *Surgical complications and recurrence rate (in surgical arm)*

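### Failed patients are censored from follow-up with no rule for them in the secondary analyses, so eyes failing before 24 months drop out of the 24-month comparisons

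*Protocol*

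**What the plan says.** The rule stands in the Analytical Plan for Trial 2, section 1 (Participant flow), b) Censoring: "Patients in both arms will be considered as failures and immediately censored when they present with 5+ lashes in the trial eye". Patients who had surgery on the trial eye from another provider likewise "will be considered as failures and immediately censored". The rule applies to the patient and sits under participant flow, not under the Cox analysis.

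Part a) of the same section lists the flowchart categories: "The numbers still in follow-up, censored, defaulting, and permanently lost-to-follow-up respectively at each visit will also be shown by arm". Censored is thus a separate state from still being in follow-up.

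The Secondary outcomes section then compares the arms at fixed late times:
- Entropion: "The effect of the intervention on the degree of entropion at 24 months will be analysed by ordered logistic regression".
- Lid margin: "The effect of the intervention on the degree of conjunctivilisation at 24 months will be analysed by ordered logistic regression".
- Cornea: "The effect of the intervention on the degree of change in CO between baseline and 24 months will be analysed by ordered logistic regression". Change at one year is also described and modelled.
- Acuity: "The effect of the intervention on the visual acuity (logMAR score) at 12 and 24 months will be analysed by linear regression".

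None of these entries says what happens to a patient censored before the visit in question.

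**The concern.** Stopping the clock at failure is correct for time to first failure. Applied to the patient, it also removes that patient from every later examination. The 24-month comparisons would then be made among eyes that had not failed earlier, a group defined by an outcome that the treatments are expected to change.

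The plan itself links that outcome to the late harms. Its justification of the primary outcome says: "Trichiasis (lashes touching the eyeball) causes visual loss through corneal opacification". The eyes lost are therefore those that the plan expects to do worst, and the arm that fails more loses more of them. Corneal change and acuity are where harm from a worse treatment would show, and this removes part of the route by which it would show. In justifying the modified intention-to-treat set, the plan recognises that missing follow-up tilts a non-inferiority trial towards non-inferiority, but it acts on this only for the primary outcome.

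**Working it through.** **Inputs from the plan.** 1300 recruited and 10% loss, so 1300 × 0.9 = 1170, or 585 per arm. Design failure rates are 5% (surgery) and 10% (epilation), with a margin of 10 points and stated power of 90% (Primary outcome, c) Sample size, Table 1). The blinded pooled failure rate is 8% (d) Statistical analysis). The pair 5% v 11% is a row of Table 2 with that pooled rate.

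**Check of the plan's own figure.** The standard error is √[(0.05 × 0.95 + 0.10 × 0.90)/585] = 0.01533. Power = Φ((0.10 − 0.05)/0.01533 − 1.96) = Φ(1.30) = 90.3%. The stated 90% reproduces, so 585 per arm and 5% v 10% are a sound base for the counts.

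**Eyes missing at 24 months.** Let f be the share of failures that occur before the 24-month visit. The loss per arm is 585 × failure rate × f. The plan gives no failure timing, so f is shown as a range.

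| f | Surgery, 5% | Epilation, 10% | Total |
|---|---|---|---|
| 0.5 | 15 | 29 | 44 |
| 0.75 | 22 | 44 | 66 |
| 1 | 29 | 59 | 88 |

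At the pooled 8% the upper bound (f = 1) is 0.08 × 1170 = 94. How those split between the arms is unknown: 47 v 47 if the arms fail equally, 29 v 64 at 5% v 11%.

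**Effect on a late outcome.** The risks here are assumptions, not figures from the plan: corneal progression in 10% of non-failures and 20% to 40% of failures, the same in both arms, with 5% v 11% failing. For failure rate p, risk r₀ in non-failures and r₁ in failures:
- everyone kept: p·r₁ + (1 − p)·r₀
- early failures lost: [p(1 − f)·r₁ + (1 − p)·r₀] / (1 − p·f)

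With r₁ = 40% and everyone kept, surgery has 0.05 × 0.40 + 0.95 × 0.10 = 11.5% and epilation 0.11 × 0.40 + 0.89 × 0.10 = 13.3%, a difference of 1.8 points. With r₁ = 20% the figures are 10.5% and 11.1%, a difference of 0.6.

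| f | Difference, r₁ = 40% | Difference, r₁ = 20% |
|---|---|---|
| 0 (everyone kept) | 1.8 points | 0.6 points |
| 0.5 | 0.105/0.975 v 0.111/0.945: 1.0 | 0.100/0.975 v 0.100/0.945: 0.3 |
| 0.75 | 0.100/0.9625 v 0.100/0.9175: 0.5 | 0.0975/0.9625 v 0.0945/0.9175: 0.2 |
| 1 | 10% v 10%: 0 | 10% v 10%: 0 |

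If failures did no worse than non-failures (r₁ = r₀), there would be no bias at any f. The illustration is for a corneal outcome. It is not meant for entropion, where surgery acts on the lid directly and the risk in non-failures need not be equal between arms.

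**Which analyses are touched.** Failure is recorded when the patient presents, so the failure visit is observed.
- 24-month entropion, lid margin, corneal change and acuity lose eyes that failed at an earlier visit. An eye first failing at 24 months can be graded there.
- 12-month acuity and one-year corneal change lose eyes that failed before 12 months.
- Lash counts lose only visits after the failure visit.
- The primary proportion loses nothing, because the failure is counted before censoring.

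**The case against.** The strongest reply is that removal from follow-up is inferred. Censoring is a time-to-event term, the plan has a Cox analysis of time to first failure, and no sentence says that failed eyes stop being examined. The visit schedule exempts no one, the lash-count analysis draws on all time points, and recurrence after surgery is estimated at each visit and counts repeat surgery. This stands to the extent that one clarifying sentence could settle the point. It does not remove the point: the rule is written for patients, the flowchart sets them apart from those in follow-up, and no late analysis says that they are kept.

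A reader might infer more than the text supports:
- That the every-visit analyses contain only patients who never failed. They do not, since the failure visit is observed.
- That 94 eyes are dropped and any difference vanishes. Both are upper bounds, reached only if every failure precedes 24 months.
- That the non-inferiority conclusion is biased. It rests on the primary proportion, which is untouched.
- That the bias must favour epilation. That follows from the design assumption that epilation fails more; only a pooled 8% is reported.

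It is also fair that the hidden difference is small against the precision available. For 11.5% v 13.3% with 585 per arm, the standard error is √[(0.115 × 0.885 + 0.133 × 0.867)/585] = 0.0193. The 95% half-width is about 3.8 points, and power to detect 1.8 points is about 15%. Keeping everyone would probably still not show a significant difference. The estimate and its interval would, however, refer to all patients as allocated.

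**Conclusion.** The point holds as a selection problem in the late secondary comparisons, on the plain reading of the censoring rule. At the design rates it costs about 44 to 88 eyes in total (f from 0.5 to 1), twice as many from epilation as from surgery; at the pooled 8% the ceiling is about 94. Under the assumed progression risks, a true difference of 0.6 to 1.8 points shrinks to 0.3 to 1.0 if half of the failures are early, and to 0 only if all are.

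This rests on three things that the plan does not give: that censored patients are not examined again, when failures occur, and that failed eyes do worse late on. The last is an inference from the plan's own causal statement. The point is worth correcting because corneal and acuity results showing no difference could be read as reassurance about harm. It gives no ground to doubt the primary analysis.

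**What to change.** 1. State that censoring applies only to the time-to-first-failure (Cox) analysis.
2. Analyse all secondary outcomes by allocated arm, including every examination made after failure.
3. Where a failed eye has no 24-month examination, run a sensitivity analysis using the grade at the failure visit or a worst-rank rule, and report it beside the main result.
4. If neither 2 nor 3 is done, label the 24-month results as conditional on not having failed earlier, and do not offer them as evidence of no corneal or visual harm.

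The plan reports a blinded end-of-trial failure rate, so follow-up appears to be over and additional examinations are not proposed. The cost is wording and one added analysis of data already recorded. There are two drawbacks: outcomes after failure include the effect of later treatment, and a carried-forward grade misses later progression. Nothing here bears on how failed eyes are treated.

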**Table 2: Examples of results, under different observed results**

| **Proportion failing in surgery arm** | **Proportion failing in epilation arm** | **Difference in proportions** | **95% CI for difference** | **Conclusions** |
| --- | --- | --- | --- | --- |
| 0% | 16% | 16% | 13.1%-19.0% | Inferior |
| 1% | 15% | 14% | 11.0%-17.0% | Inferior |
| 2% | 14% | 12% | 9.0%-15.0% | Inconclusive |
| 3% | 13% | 10% | 6.9%-13.1% | Inconclusive |
| 4% | 12% | 8% | 4.9%-11.1% | Inconclusive |
| 4.5% | 11.5% | 7% | 3.9%-10.1% | Borderline non-inferior |
| 5% | 11% | 6% | 2.9%-9.1% | Non-inferior |
| 6% | 10% | 4% | 0.9%-7.1% | Non-inferior |
| 7% | 9% | 2% | -1.1%-5.1% | Non-inferior |
| 8% | 8% | 0% | -3.1%-3.1% | Non-inferior |

*e) Primary analysis*

Our primary analysis will be a modified intention to treat (ITT) analysis, which will include only those individuals who were seen at least once.

*Justification for using modified ITT:*

In a trial comparing two drug treatments a per-protocol analysis would be used to try to determine the ‘true’ effect of the drug treatment (excluding for example issues of drug compliance), by only analysing the participants who follow their treatment allocation. However, it is not appropriate in the present study, which compares a one-off treatment (surgery), in which all participants follow their treatment allocation, with a repeated treatment (epilation), in which participants may not adhere. Therefore, a per-protocol analysis would require the comparison of all participants in one arm with a biased selection from the other arm. The per-protocol analysis would require exclusion of individuals not epilating in the epilation arm. However, some of these individuals may have epilated once or twice and found the lashes not to recur, thus obviating the need to epilate. These people are treatment successes and it would be wrong to exclude them from the analysis.

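### Table 2 labels a result with upper limit 10.1% borderline non-inferior, against the plan's below-10% rule, and the 4.5% cut-off comes from Wald limits although exact ones are specified

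*Protocol*

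**What the plan says.** All references are to the Analytical Plan for Trial 2 in the Protocol, under Primary outcome.

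- **Rule.** Section d) Statistical analysis: "Non-inferiority of epilation will be shown if the upper two-sided 95%CI around the estimated difference in proportions is below 10" per cent. Section c) Sample size states the same criterion.
- **Method.** Section d) calls for the "95%CI for this difference using exact methods". No particular exact method is named.
- **Cut-off.** Section d) reports that "Blinded analyses conducted at the end of the trial showed an overall failure rate of 8" per cent and then says that, at this rate, "the conclusion will be that epilation is non-inferior to surgery if the proportion failing in the surgery arm is greater than 4.5" per cent. It also calls epilation inferior at an epilation-arm failure rate of 15% or more.
- **Table 2.** The 4.5% v 11.5% row reads "3.9%-10.1% | Borderline non-inferior". The row above it, 4% v 12% with upper limit 11.1%, is labelled inconclusive.
- **Table 1.** Powers are given for a "sample size of 585 per arm (1300 recruited, 10% loss to follow-up"). The row with 3% v 9% failing and a 10-point margin states 85%.
- **Analysis set.** Section e) Primary analysis includes everyone seen at least once.

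**The concern.** An upper limit of 10.1% is not below 10%. The rule leaves no room for a borderline category, so the label describes as a qualified pass a result that the rule does not pass.

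The cut-off is worded as a conclusion that will be drawn, not as an example. If it comes from a different interval method from the one prescribed, the plan holds two criteria that can disagree close to the boundary. The section was written with the pooled failure rate already known, so the verdict rests on how the failures split between the arms. That is where two competing criteria do most harm.

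**Working it through.** **Inputs.** Margin 10 points and two-sided 95% limits (section d). One-sided alpha 0.025 (closing Sample size section). 585 per arm (Table 1). Pooled failure rate 8% (section d), so the two arm rates sum to 16%. Assumption: equal arms. Expected failures at 585 per arm: 0.08 × 1170 = 93.6, taken as 94.

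**Step 1: reproduce Table 2.** The Wald limits are d ± 1.96 × √{[p_S(1 − p_S) + p_E(1 − p_E)]/n}. For 4.5% v 11.5%:

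- variance sum: 0.042975 + 0.101775 = 0.14475
- SE: √(0.14475/585) = 0.01573
- limits: 7.00% ± 3.08% = 3.92% to 10.08%, printed as 3.9%-10.1%

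At n = 585 the formula matches nine of the ten rows to one decimal. In the 0% v 16% row only the lower limit differs (13.03% against 13.1%). Table 2 is therefore a Wald table.

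**Step 2: locate the cut-off.** Solve (0.16 − 2p) + 1.96 × √{[p(1 − p) + (0.16 − p)(0.84 + p)]/n} = 0.10 for the surgery rate p. At n = 585, p = 4.54%, which is the source of the printed 4.5%. At n = 650, p = 4.46%.

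**Step 3: compare with exact limits.** The check is an unconditional exact test of a difference of 10 points or more, maximised over the unknown surgery rate, with limits found by inverting the test. Outcomes are ordered by the score statistic.

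| n per arm | Surgery v epilation failures | Rates | Wald upper | Exact p | Exact upper |
|---|---|---|---|---|---|
| 585 | 26 v 68 | 4.44% v 11.62% | 10.27% | 0.044 | 10.41% |
| 585 | 27 v 67 | 4.62% v 11.45% | 9.93% | 0.0275 | 10.07% |
| 585 | 28 v 66 | 4.79% v 11.28% | 9.59% | 0.017 | 9.74% |
| 650 | 30 v 74 | 4.62% v 11.38% | 9.70% | 0.019 | 9.83% |

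The second row is the first attainable result above 4.5% at 585 per arm. The cut-off sentence passes it; the score-ordered exact test does not.

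Ordering by the raw difference, another exact choice, gives 27 v 67 an upper limit of 12.62% and first passes at 35/585 = 5.98%. At 650 per arm it gives 30 v 74 an upper limit of 12.25% and first passes at 38/650 = 5.85%.

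**Step 4: rounding of the pooled rate.** If 8% stands for anything from 7.5% to 8.49%, the Wald boundary at 585 per arm runs from about 4.0% to 5.1%.

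**Step 5: Table 1.** The printed formula is not legible in the document. The usual normal form for the quantities that it lists is power = Φ[(Δ − µ)/SE − 1.96], with the SE as in step 1.

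- Design row (5% v 10%, margin 10): SE = √(0.1375/585) = 0.01533; 0.05/0.01533 − 1.96 = 1.30; power 90.3%. The plan says that its sample "would provide 90% power to detect non-inferiority", so this reproduces.
- Row 3% v 9%, margin 10: SE = √[(0.0291 + 0.0819)/585] = 0.01377; 0.04/0.01377 − 1.96 = 0.944; power 82.7%, against the stated 85%.
- The other ten rows, the design row included, agree to within 1 percentage point.

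**The case against.** The strongest reply is that the governing rule is clear. It appears in sections c) and d), Table 2 is titled as a set of examples, and any reported interval would show whether its upper limit was below 10%. That stands, and it limits the consequence. It does not make the label right.

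A reader might infer four stronger points, which the documents do not support.

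- **That the cut-off sentence itself passes the 10.1% row.** It says greater than 4.5%, which excludes that row. On the Wald basis it sorts every attainable count at 585 per arm correctly: 26 v 68 fails and 27 v 67 passes.
- **That the cut-off fails under the exact method specified.** No method is specified beyond the word exact. With score ordering the failure at 585 is a single split, missing by 0.07 points. Section e) allows the analysed n to lie between 585 and 650, and at 650 the first split above 4.5% passes with score ordering, though not with difference ordering.
- **That the 15% cut-off is also wrong.** It is a sufficient condition. The Wald lower limit reaches 10% at 14.5% epilation failure, so 15% is a cautious rounding. At 6 v 88 (15.04%) the Wald limits are 11.0% to 17.0%, and the score-ordered exact p is 0.003. Only difference ordering disagrees (p = 0.088).
- **That 5% v 11% is mislabelled.** The row reads "2.9%-9.1% | Non-inferior" and follows the rule. Adding that the interval excludes zero would be a reporting choice.

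**Conclusion.** The point holds on three counts.

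1. The label on the 4.5% v 11.5% row contradicts the stated rule. This needs no assumption.
2. Table 2 and the 4.5% cut-off come from Wald limits at 585 per arm, while the plan prescribes exact ones. At 585 per arm and 94 failures, the cut-off and a score-ordered exact test disagree on one split, 27 v 67. This assumes equal arms, a pooled rate of 8% and that choice of ordering. The disagreement disappears at 650 per arm with score ordering and widens with difference ordering. The rounding of 8% moves the boundary by more than the gap between Wald and score-ordered exact limits. A fixed cut-off therefore cannot stand in for the interval rule.
3. One secondary power in Table 1 is overstated by about 2 points (85% against 82.7%). The design row is unaffected.

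A reader might infer a flaw in the design or in the primary test. There is none here: the margin and the interval rule are untouched, and the planned 90% power reproduces. This is a minor to moderate text correction.

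**What to change.** - Relabel the 4.5% v 11.5% row of Table 2 as inconclusive.
- Name the exact interval method, including how outcomes are ordered. Regenerate Table 2 and the 4.5% cut-off with it at the actual analysed n per arm and the unrounded pooled rate, or delete the cut-off sentence.
- State that the upper-limit-below-10% rule alone decides non-inferiority and that Table 2 is illustrative.
- Correct the Table 1 entry for 3% v 9% with a 10-point margin from 85% to 83%.

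The cost is text edits and one recomputed table. At 585 per arm a regenerated cut-off would be slightly stricter with score ordering (first pass at 4.79%) and clearly stricter with difference ordering (5.98%). The method should therefore be chosen and recorded before the split by arm is seen.
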